## Assignment of interventions: blinding

### Who will be blinded {17a}

Randomization takes place after baseline. Study staff from each study center who measure post-treatment (T1) and follow-up (T2) are blinded regarding group assignment. Rater and therapy rooms are far apart, to support the blinding of the raters throughout the whole course of the study. Raters log at the measurement time points T1 and T2 for each study participant whether they are blinded or not. Due to study design and significantly different interventions in the study arms, therapists, study participants, and additional persons who are responsible for the external assessment for social responsiveness are not blinded. The biometrician and his representative will remain blinded until data base closure.

### Procedure for unblinding if needed {17b}

No procedure for unblinding of therapists is necessary. Therapists always have information about the allocation of each study participant. If unblinding of raters takes place by accident, the unblinding is recorded and another rater will perform the future measurements (T1 or T2).

## Data collection and management

### Plans for assessment and collection of outcomes {18a}

A detailed description of the study instruments and their validity can be found in the section “Outcomes”.

Raters are trained for 2 days in the Structured Clinical Interview for DSM-5 for clinical diseases (SCID-5-CV), the Autism Diagnostic Observation Scale (ADOS-2), the Global Assessment of Functioning (GAF), the Multifaceted Empathy Test (MET, computer test) and IQ testing for the Culture Fair Intelligence Test (CFT 20-R) and the complete process of data acquisition.

Additionally, all trained procedures are video recorded and are available via Internet access for all raters. Also available are frequently asked questions about the procedures via Internet access. Monthly supervisions via video conference will be held for best knowledge approximation between centers.

If new raters have to be trained, they will use the video-recorded information about training and take also part in the monthly supervisions via video-conference.

Therapists for FASTER and SCOTT&EVA are trained for 2 days regarding all sessions and procedures. Additionally, all trained procedures are video-recorded and are available for all therapists via Internet access. Frequently asked questions about the procedures are also available via Internet access. Monthly supervisions via video conference are offered for best knowledge approximation between centers.

If new therapists have to be trained, they use the video-recorded information about training and take also part in the monthly supervisions via video conference.

The training measures for raters and therapists of the study are documented in training logs. Raters and therapists can only be accepted into the study team after successful completion of the training. The recording must be authorized by the center’s principal auditor. The training logs are checked via the monitoring visits.

Data collection forms for each center can be found in the investigator site file (ISF) as well as in an internet-based platform that is accessible to all raters and therapists. In addition, frequently asked questions (FAQ) about study contents are available for all participating members of the study centers.

### Plans to promote participant retention and complete follow-up {18b}

Between T1 and T2, both FASTER and SCOTT&EVA participants are offered monthly refresher sessions in the respective study center. The refresher sessions are implemented to support the transfer of skills and knowledge gained during the intervention phase into daily life.

TAU patients are offered a compensatory FASTER or SCOTT&EVA program after completion of their trial participation. SCOTT&EVA participants will also be offered an additional FASTER group therapy after completion of their trial participation if requested. Currently, there are few treatment options for the study participant group, so participation in this study is most likely motivating. In case of protocol violations or withdrawals, the subjects will still take part in the further assessments if they do not deliberately resign also from the follow-up assessments.

### Data management {19}

Case report forms (CRFs) are paper-based. Source data will be collected in each center from the rating and therapy staff and will be transferred into the CRFs. Source data is stored in the respective center. Source data and transmission to the CRFs will be checked via monitoring by on-site visits in each study center. A copy of each CRF will be made and the original will be sent to the Institute of Medical Biometry and Informatics (IMBI, Heidelberg).

The Institute of Medical Biometry and Informatics (IMBI, University Hospital Heidelberg) is responsible for the data management within the trial. In order to ensure that the database reproduces the case report forms (CRF) correctly, the IMBI accomplishes a double entry of data. In order to guarantee high quality of data, the completeness, validity, and plausibility of data as defined in a data validation plan will be checked using validating programs, which will generate queries. A tracking system for CRF data and queries will be established to guarantee that data is managed in a timely manner. The investigator or the designated representatives are obliged to clarify or explain the queries. If no further corrections are to be made in the database it will be closed and used for statistical analysis. All data management procedures will be carried out on validated systems and according to the current Standard Operating Procedures (SOP) of the IMBI that guarantee an efficient conduct which is in compliance with GCP.

At the end of the study, the data will be transformed into different data formats (e.g., csv-files) to ensure that it will be possible to reuse it. The principle investigator will retain the originals of all CRFs and the trial data for long-term preservation. After completion of the study, we plan to make the publication data and the primary data publicly available for re- and meta-analyses.

### Confidentiality {27}

The data obtained in the course of the trial will be treated pursuant to the Federal Data Protection Law (Bundesdatenschutzgesetz, BDSG).

During the clinical trial, subjects will be identified solely by means of their individual identification code (screening number, randomization number). Trial findings stored on a computer will be stored in accordance with local data protection law and will be handled in strictest confidence. Distribution of these data to unauthorized persons is strictly prevented. The appropriate regulations of local data legislation will be fulfilled in its entirety.

The subject consents in writing to release the investigator from his/her professional discretion in so far as to allow inspection of original data for monitoring purposes by authorized persons (monitors, auditors). Authorized persons (clinical monitors, auditors) may inspect the subject-related data collected during the trial ensuring the applicable data protection law.

The investigator will maintain a subject identification list (subject numbers with the corresponding subject names) to enable records to be identified. Subjects who did not consent to circulating their pseudonymized data will not be included into the trial.

This protocol, the CRFs, and other trial-related documents and material will be handled with strictly confidentiality and will not be disclosed to third parties except with the express prior consent of the Lead Investigator. Staff of the investigators involved in this study are also bound by this agreement.

### Plans for collection, laboratory evaluation, and storage of biological specimens for genetic or molecular analysis in this trial/future use {33}

There will be no biological specimens collected (see the “Additional consent provisions for collection and use of participant data and biological specimens {26b}” section above).

## Statistical methods

### Statistical methods for primary and secondary outcomes {20a}

#### Trial populations to be analyzed

The primary analysis will be performed for the full analysis set which comprises all patients randomized into the trial. In this set, every patient is analyzed according to the randomized group.

The per-protocol set will comprise all patients who were treated according to the randomized treatment without further major protocol violations.

The safety set will comprise all patients of the full analysis set and will allocate the patients to the treatment they actually received, regardless of randomization.

The allocation of each patient to the different study populations will be defined and explained in further detail in the statistical analysis plan (SAP).

#### Estimands

In the recently released ICH E9 (R1) addendum on estimands and sensitivity analysis in clinical trials, the estimands framework is recommended as clear and transparent definition of “a structured framework to strengthen the dialogue between disciplines involved in the formulation of clinical trial objectives, design, conduct, analysis and interpretation, as well as between sponsor and regulator regarding the treatment effect(s) of interest that a clinical trial should address” [46]. Such an estimand can be defined through the population of interest, variable of interest, specification of how intercurrent events are handled, and summary measure. The specification of how intercurrent events are handled is referred to as intervention effect in the following. This way, a more precise definition of the treatment effect of interest in relation to the study objective(s) is enabled. Based on such an estimand, adequate methods to estimate this estimand can be chosen. In the following, the primary estimand corresponding to the primary objective is described. If unforeseen intercurrent events will occur frequently during the course of the trial, they will be specified in the statistical analysis plan. By only reporting pooled data without information on the treatment group allocation to the supervising and the study biometrician until the database is locked, blinding will be maintained. In the statistical analysis plan, further sensitivity estimands will also be described.

#### Primary estimand

##### Population

The population is defined through appropriate inclusion/exclusion criteria to reflect the targeted patient population.

##### Variable

The variable is the SRS-A score (parent/spouse/other).

##### Intervention effect

Possible intercurrent events and the strategies to handle them are as follows. Serious adverse events and adverse events will be ignored for the primary analysis (treatment policy strategy). The same strategy will be applied for all other intercurrent events as, e.g., treatment withdrawal or unforeseen in-patient stay.

##### Summary measure

The summary measure is the difference in the SRS-A (parent/spouse/other) between 4 months after baseline (T1) and the baseline value (T0). The applied test is described in the next subsection.

#### Analysis

Let μ denote the unknown true mean difference of the SRS-A score between baseline and 4 months after baseline. The following two primary local test problems are assessed:
$$ {\mathrm{H}}_{0,\mathrm{SCOTT}\&\mathrm{EVA}}:{\upmu}_{\mathrm{SCOTT}\&\mathrm{EVA}}={\upmu}_{\mathrm{TAU}}\ \mathrm{versus}\ {\mathrm{H}}_1:{\upmu}_{\mathrm{SCOTT}\&\mathrm{EVA}}\ne {\upmu}_{\mathrm{TAU}} $$

and
$$ {\mathrm{H}}_{0,\mathrm{FASTER}}:{\upmu}_{\mathrm{FASTER}}={\upmu}_{\mathrm{TAU}}\ \mathrm{versus}\ {\mathrm{H}}_1:{\upmu}_{\mathrm{FASTER}}\ne {\upmu}_{\mathrm{TAU}} $$

The aim is to show that at least one of the two local alternative hypotheses holds true. For each pairwise comparison (TAU versus FASTER and TAU versus SCOTT&EVA) a Mixed Model Repeated Measures (MMRM) will be applied. It includes the difference of the SRS-A score between baseline and 4 months after baseline as the dependent variable, the baseline SRS-A score, and the group allocation as fixed effects, and the center and the cluster as random effects. The MMRM uses all available changes from baseline SRS-A score for all patients for model estimation. In the “Sample size {14}” section, the local significance level of .026632 has been deduced. In case that at least one of the null hypotheses specified above can be rejected at the local significance levels of .026632, we hierarchically assess additionally the following test problem:
$$ {\mathrm{H}}_{0,\mathrm{SCOFA}}:{\upmu}_{\mathrm{SCOTT}\&\mathrm{EVA}}={\upmu}_{\mathrm{FASTER}}\ \mathrm{versus}\ {\mathrm{H}}_1:{\upmu}_{\mathrm{SCOTT}\&\mathrm{EVA}}\ne {\upmu}_{\mathrm{FASTER}} $$

at the full two-sided level of 0.05 in a confirmatory manner. In case neither H0, SCOTT&EVA nor H0, FASTER can be rejected, the comparison between the FASTER and the SCOTT&EVA arm is done descriptively. The confirmatory analysis of the primary efficacy endpoint corresponds to the primary estimand and will be conducted in the full analysis set.

As a sensitivity analysis to the primary efficacy analysis, corresponding MMRMs with additional covariates/factors given by IQ, age, gender, ASD symptom severity, MET test result, and center will be conducted. Furthermore, the separate items of the SRS-A score are analyzed individually to investigate which items differ between the treatment groups. Details of these analyses will be specified in the statistical analysis plan (SAP).

Exploratory analyses will investigate moderation of treatment effects by conducting the primary MMRM considering the following additional variables: IQ, age, gender, center, years of therapy experience with autism, depressiveness (BDI), self-confidence (MSWS), social competence (SASKO), and life events (FEL). To optimize treatment selection for individual patients, these covariates will be used to estimate individualized treatment effects from parameter estimates to construct optimal individualized treatment rules and to clarify for whom a treatment works best [47].

Descriptive methods will be used for the analysis of the secondary outcomes, including the calculation of appropriate summary measures of the empirical distribution as mean, median, standard deviation, 1st and 3rd quantile for continuous outcomes, and absolute and relative frequencies for count data. Furthermore, 95% confidence intervals and descriptive two-sided *p*-values will be reported. Graphical methods will be applied to visualize the findings. The safety analysis includes calculation of frequencies and rates of adverse and serious adverse events. Additionally, as supplementary analysis the primary endpoint will be evaluated in the per-protocol population. Furthermore, statistical methods are used to assess the quality of data. All analyses will be done using Statistical Analysis Software (SAS) version 9.4 or higher.

Analyses will be defined in detail in the SAP which has to be authorized before data base closure by the two involved biometricians and the lead investigator.

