### Outcomes {12}

All outcomes will be assessed at baseline (T0), post-treatment (T1, 4 months after baseline), and follow-up (T2, 8 months after baseline).

The primary endpoint of our trial is the change of the total sum score from baseline (T0) to 4 months after baseline (T1) in social responsiveness as measured with the *Social Responsiveness Scale* (SRS-A adult, parent/spouse/other, [18, 19]).

The secondary outcome measures aim to differentially assess aspects of self-reported social responsiveness, social cognition, social skills, empathy, common comorbid psychopathology, self-esteem, life satisfaction, and quality of life. Almost all questionnaires and tests (see Table 1) are well-established, widely-used instruments with excellent psychometric properties (see also the “Data collection and management” section).

The measurement for social responsiveness (parent/spouse/other) at the follow-up measurement time point (T2) is also a secondary outcome.

**Table 1 Tab1:** Illustration of frequency of study visits, questionnaires, and tests

	SCR	T0	T1	T2
GAF (SCR: via telephone or personally)	x^1^	x^3^	x	x
Psychopharmacotherapy	x^1^	x	x	x
ADOS-2 (if lacking)	x^2^			
SCID-5-CV	x^2^			
CFT 20-R	x^2^			
MWT-B	x^2^			
Neo-FFI	x^2^			
AQ50	x^2^			
EQ40	x^2^			
WURS-K	x^2^			
ADHS-SB	x^2^			
TAS-26	x^2^			
Basis Documentation	x^2^			
SRS-A (patient)		x	x	x
SRS-A (parent/spouse/other)		x	x	x
SRS-A mod. (patient)			x	x
SRS-A mod. (parent/spouse/other)			x	x
MET (computer test)		x	x	x
BDI-II		x	x	x
SASKO		x	x	x
MSWS		x	x	x
FLZ^M^		x	x	x
WHOQoL-Bref		x	x	x
Freiburg Event List			x	x
Partnership Questionnaire (if appropriate)		x	x	x

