### Methods in analysis to handle protocol non-adherence and any statistical methods to handle missing data {20c}

The trial populations including the per protocol analysis set are defined in the section “Statistical methods”.

The MMRM applied for the analysis of the primary endpoint takes into account missing data. It uses all available changes from baseline SRS-A score for all patients for model estimation. If a patient has a missing change from baseline SRS-A score, the model assumes that the patient’s missing SRS-A score is comparable to the observed SRS-A score of another patient having similar baseline characteristics and a comparable course of change from baseline.

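### The primary MMRM is specified with one response per patient, so it is a mixed-model ANCOVA on observed T1 changes and lacks the missing-data property claimed for it

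*Protocol article*

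**What the plan says.** All statements are in the protocol article; SRS-A here means the version completed by a parent, spouse or other informant.

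- **Response (Analysis).** "It includes the difference of the SRS-A score between baseline and 4 months after baseline as the dependent variable".
- **Terms (Analysis).** The model has "the baseline SRS-A score, and the group allocation as fixed effects, and the center and the cluster as random effects". No other term is listed.
- **Data used (Analysis).** "The MMRM uses all available changes from baseline SRS-A score for all patients for model estimation". The visits are not named.
- **Missing data ({20c}).** "The MMRM applied for the analysis of the primary endpoint takes into account missing data". A missing score is assumed to be like that of another patient "having similar baseline characteristics and a comparable course of change from baseline".
- **Analysis set (Trial populations to be analyzed).** "The primary analysis will be performed for the full analysis set which comprises all patients randomized into the trial".
- **Role of T2 (Outcomes {12}).** "The measurement for social responsiveness (parent/spouse/other) at the follow-up measurement time point (T2) is also a secondary outcome".

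The hypotheses in the Analysis section and the Summary measure of the primary estimand both concern the change from baseline to T1. The estimand uses a treatment-policy strategy for every intercurrent event. Sample size {14} computes N from an ANCOVA and treats the MMRM as a different but comparable model.

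**The concern.** An MMRM earns its name, and its missing-data behaviour, from repeated responses per patient linked by a within-patient covariance. A patient with T2 but no T1 then contributes to the T1 estimate through the T2 value. The model in the Analysis section has one response per patient and nothing to link, so such a patient drops out of the confirmatory test even though the T2 form is already scheduled.

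Two things are at stake. First, the confirmatory analysis is announced for all randomized patients under treatment policy, with a missing-data rationale that the specified model does not have. Second, the text can be programmed in two ways that test different effects. The primary outcome comes from an informant who is not blinded (Who will be blinded {17a}), so form return could plausibly differ by arm. It therefore matters which missingness assumption is really being made.

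**Working it through.** **1. Responses per patient.** The only response named is the T0-to-T1 change. One row per patient leaves no within-patient covariance to estimate and no visit factor to fit. What remains is change = baseline SRS-A + group + random center + random cluster: an ANCOVA with random effects.

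**2. Does a patient without T1 contribute?** A model of this type (cluster random effect only) was fitted to one simulated two-arm data set of 240 patients in clusters of 6, with about 25% of changes missing. Keeping or deleting the incomplete rows gave the same fit: 183 rows used, estimate -0.3445, SE 0.1239. Such patients add nothing.

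**3. What the model does assume.** Large-sample check, true effect -0.40 SD, baseline-to-T1 correlation 0.2 (Sample size {14}). The estimate is -0.398 under completely random loss and -0.398 when loss depends on baseline and arm. The analysis is therefore valid if missingness depends only on the terms in the model. The part of {20c} about similar baseline characteristics holds for baseline SRS-A; the part about the course of change does not.

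**4. The plan's own sample size.** Inputs from Sample size {14}: effect 0.4 for both comparisons, correlation 0.2, design effects 1.05 (TAU, SCOTT&EVA) and 1.25 (FASTER), test correlation 0.455, local level 0.026632 (critical value 2.217).

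Mean of each test statistic = 0.4 / sqrt[(1 - 0.2²) × (1.05 + DE) / n]

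- n = 87: means 2.628 (SCOTT&EVA) and 2.511 (FASTER); power for at least one comparison 0.8015. The stated 87 is reproduced.
- Drop-out: 87 / 0.75 = 116, rounded up to 120 as a multiple of 6. Also reproduced.
- At 25% loss: 120 × 0.75 = 90 per arm, power 0.815. At 20%: 96 per arm, power 0.839. With all 120 observed: 0.911.

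Dropping patients without T1 is thus what the sample size already assumes.

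**5. Possible bias (illustration).** Assumptions not in the documents: 25% missing in each arm, missingness depending on T1 self-report with log-odds 0.3, 0.6 or 1.0 per SD, and self-report/informant correlation 0.5. True effect -0.40 SD.

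| Outcome-related loss | 0.3 | 0.6 | 1.0 |
|---|---|---|---|
| Active arm only, random loss in TAU | about -0.44 | -0.47 | -0.50 |
| Same mechanism in both arms | -0.40 | -0.40 | -0.40 |

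The range runs from no bias to about 0.04–0.10 SD.

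**6. The other reading: T1 and T2 changes both enter.** With group as the only treatment term, the coefficient is an average over the two visits, roughly (effect at T1 + effect at T2) / 2. That equals the T1 effect only if the two effects are equal. The documents give no T2 effect. If it were half the T1 effect, the tested effect would be (0.4 + 0.2) / 2 = 0.30. The variance of a two-visit mean is 0.96 × (1 + r) / 2, with r the residual T1–T2 correlation. At n = 87, power for at least one comparison is then 0.74, 0.68, 0.62 and 0.58 for r = 0.3, 0.5, 0.7 and 0.9.

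**The case against.** The best defence is that a journal article condenses. The plural in "The MMRM uses all available changes from baseline SRS-A score for all patients for model estimation" and the mention of a course of change suggest that a conventional T1-and-T2 MMRM was meant. Visit terms and covariance structure are ordinary SAP detail, and the article defers detail to a SAP authorized before database closure. The hypotheses and summary measure already fix T1 as the target.

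Part of this stands. Silence about a covariance structure would be no finding. But the article is not silent: it names one response, lists the terms, and then claims a property that this model lacks. Adding T2 to the listed terms does not reconcile the sections either, because the group effect would no longer be the T1 effect in the hypotheses.

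Four stronger readings are tempting and are not supported:

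- **That missing data are not handled at all.** The model is valid under missingness that depends only on baseline SRS-A, group, center and cluster.
- **That a quarter of the patients and the power are lost.** The 25% is a planning figure described as conservative, patients who stop treatment are still to be assessed at T1 and T2 ({11b}, {18b}), and the loss is already in N.
- **That the estimate will be biased.** This needs outcome-related loss that differs between arms. Nothing in the documents shows it, and the same loss in both arms gave no bias.
- **That stacking T2 cuts power to 0.55.** That figure assumes a halved T2 effect and keeps the single-visit variance, which amounts to a T1–T2 correlation of 1. The protocol's own estimate over 9 months is .27, although with a wide interval.

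**Conclusion.** The point holds as an internal contradiction in the confirmatory analysis. The specified model is a mixed-model ANCOVA on patients with an observed T1 informant SRS-A. It cannot use a course of change, and it discards patients who have T2 but not T1. Neither reading of the text makes the Analysis section, {20c} and the T1 hypotheses agree.

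Planned power is not at issue: 90 evaluable per arm against 87 needed, power 0.815 under the protocol's assumptions. The consequence for the estimate is conditional. It ranges from no bias, when the mechanism is the same in both arms, to about 0.04–0.10 SD against an assumed effect of 0.40 SD, when outcome-related loss occurs in one arm only. That upper range rests on the illustrative assumptions in step 5 and is not a forecast.

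**What to change.** Specify the primary model as follows:

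- **Responses:** the changes from baseline at T1 and at T2.
- **Fixed effects:** arm, visit, arm-by-visit, baseline SRS-A and baseline-by-visit.
- **Covariance:** unstructured within patient, with random center and cluster.
- **Primary test:** the arm contrast at T1.

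Then rewrite {20c} so that it describes this model's assumption.

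Multiple imputation using T1 self-report SRS-A, GAF, BDI-II and T2 informant SRS-A may be added as a sensitivity analysis for patients whose informant form is missing. It is optional.

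The limits should be stated. The two-visit model helps only patients with T2 but no T1. Neither step repairs the loss of all data from T1 onward, or missingness that depends on unobserved scores.

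The cost is protocol and SAP wording and some programming. All the data are already scheduled in Table 1. The wording should be settled before the SAP is authorized, because the two current readings test different effects.

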### Objectives {7}

The main objective of this trial is to prove the effectiveness and efficacy of the therapy programs FASTER and SCOTT&EVA in a combined phase-III trial.

The primary hypothesis is if there is superiority of at least one of the treatments FASTER and SCOTT&EVA over treatment as usual (TAU) regarding social responsiveness.

If this is confirmed, the difference between FASTER and SCOTT&EVA regarding the primary endpoint will be tested confirmatorily. Otherwise, the comparison between FASTER and SCOTT&EVA will be done descriptively.

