### Sample size {14}

The sample size calculation is based on the primary outcome measure “mean difference of the SRS-A score between baseline and 4 months after baseline”. The aim is to show that at least one of the two treatment protocols (SCOTT&EVA or FASTER) is superior to TAU which results in a union-intersection test. The sample size calculation is based on an ANCOVA model adjusted for the baseline SRS-A score. Since both models are well comparable, the power of the finally applied mixed model repeated measures (MMRM) is expected to be close to the intended value used for sample size calculation based on an ANCOVA. To obtain an estimate for the correlation between baseline and 4-months value, we analyzed internal data of 17 patients with a time difference of 9 months between measurements of SRS-A score. This yielded a correlation coefficient of .27 (95% CI [−.24; .66]). Hence, we use a conservative correlation of .2 for sample size calculation. The standardized treatment effects for SCOTT&EVA versus TAU and FASTER versus TAU are both assumed to be equal to 0.4. These prior assumptions are based on previous research results [43].

The global two-sided significance level is 0.05. The two test statistics referring to the comparison of TAU versus SCOTT&EVA and TAU versus FASTER are correlated due to the common comparator TAU. This correlation is determined by the ratio of variances of the group effect estimators. We assume equal variances in TAU and SCOTT&EVA and a small intra-group correlation of 0.05 in FASTER. Since SCOTT&EVA and TAU are no group therapies, we expect, if at all, a very small intra-group correlation caused by cluster randomization. Conservatively, we assume an intra-group correlation of 0.01 in these treatments. This results in a design effect of 1.25 inflating the variance in FASTER and a design effect of 1.05 inflating the variances in SCOTT&EVA and TAU. Hence, the correlation of test statistics is given by $$ \frac{1}{\sqrt{\left(1.05+1.05\right)\bullet \left(1.05+1.25\right)}}=0.455 $$. The correlation-adjusted local significance levels are computed from a bivariate normal distribution and are given by 0.026632 [44]. Applying these local levels guarantees that the family-wise error rate is controlled by the global two-sided significance level of 0.05.

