## Discussion

The purpose of this study is to validate existing data for the two different treatment concepts FASTER and SCOTT&EVA in a multi-center, randomized phase-III trial. FASTER and SCOTT&EVA concepts are among the most elaborated German treatment concepts for adults with ASD in line with modern therapy standards and have demonstrated feasibility and yielded good phase-II data. The study protocol meets the essential standards of modern research in psychotherapy. Since the required sample size to find a significant effect with a power of 0.8 is given by 87 patients per group, a number of 120 participants per group and a total sample size of 360 participants will be sufficient to find an effect (assuming there is one). In order to minimize the differences among groups, the participants will be randomized to treatment and control conditions (randomized controlled trial). The use of standardized diagnostic instruments for the assessment of eligibility as well as primary and secondary efficacy analysis facilitates ecologically valid outcomes. A defined primary endpoint before trial initiation and a registration at Current Controlled Trials on the German Clinical Trials Register (http://www.drks.de) ensure both the validity of the methodical procedure as well as the transparency of the whole trial for the scientific community and is a prerequisite for future publications in peer-reviewed journals. A comprehensive independent monitoring strategy including on-site visits and frequent communication according to the standard operating procedure of the Coordination Center for Clinical Trials, Heidelberg will assure data quality and security of patients. In consideration of reducing experimental biases, data collectors of each center (rating staff) are blinded in this study and separated from therapists or other intervention related work. Thus, they will have no knowledge about individual group assignment. Both intervention programs will be implemented by trained therapists with clinical background. Using intention-to-treat-analyses and per-protocol-analyses, the study represents a conservative and clinically useful strategy of data analysis.

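### Once one TAU comparison is rejected, the other could also be tested at 0.05: the testing rule in the Analysis section is valid but needlessly conservative

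*Protocol article*

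**What the plan says.** In the protocol article, Sample size {14} sets the error budget: "The global two-sided significance level is 0.05". It then splits this over the two comparisons with TAU: "The correlation-adjusted local significance levels are computed from a bivariate normal distribution and are given by 0.026632", and adds "Applying these local levels guarantees that the family-wise error rate is controlled by the global two-sided significance level of 0.05".

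The Analysis section applies that level to both TAU comparisons. Its success criterion is disjunctive: "The aim is to show that at least one of the two local alternative hypotheses holds true". The next step is conditional: "In case that at least one of the null hypotheses specified above can be rejected at the local significance levels of .026632", SCOTT&EVA versus FASTER is tested "at the full two-sided level of 0.05 in a confirmatory manner". Nothing is said about raising the level for the TAU comparison that has not been rejected, so it remains at 0.026632.

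Two other places bear on the point. Objectives {7} opens with: "The main objective of this trial is to prove the effectiveness and efficacy of the therapy programs FASTER and SCOTT&EVA"; its next sentence narrows the primary hypothesis to superiority of at least one program. The Discussion says that the planned numbers "will be sufficient to find an effect (assuming there is one".

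**The concern.** After the gate has opened, the plan treats the two remaining comparisons differently. FASTER versus SCOTT&EVA receives 0.05; the second TAU comparison does not. The reasoning that justifies the first release justifies the second as well. A program with a p-value between 0.026632 and 0.05 against TAU would therefore miss formal significance although the other program had passed, and although testing it at 0.05 would keep the FWER within 0.05. The stake is the chance of a confirmatory statement on both programs. The primary criterion is not affected.

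**Working it through.** **Inputs (Sample size {14}).** Global two-sided level 0.05; local level 0.026632; standardized effect 0.4 for each program versus TAU; baseline correlation 0.2, so ANCOVA variance factor 1 − 0.2² = 0.96; design effects 1.25 (FASTER) and 1.05 (SCOTT&EVA, TAU); 87 per group; 25% drop-out; 120 randomized per group.

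**Reproducing the plan's figures.**
- With the stated correlation 1/√(2.1 × 2.3) = 0.455, solving 1 − P(|Z₁| < c, |Z₂| < c) = 0.05 gives c = 2.2169, a local level of 0.02663. This agrees with the plan.
- Expected test statistics at n = 87: FASTER 0.4/√(0.96 × 2.30/87) = 2.511; SCOTT&EVA 0.4/√(0.96 × 2.10/87) = 2.628.
- Power for at least one rejection is 0.8015, and 87 is the smallest n that reaches 0.80. This agrees with the plan.
- 87/(1 − 0.25) = 116, raised to 120 for clusters of six.

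The simulation below draws three arm means with the stated variances. That implies a correlation of 1.05/√(2.1 × 2.3) = 0.478 rather than 0.455, so at-least-one power appears as 0.798 instead of 0.8015. The difference does not affect the comparison of the two rules.

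**Why the release is allowed.** Any two of the three equalities imply the third. So the set of true nulls is all three, exactly one, or none.
- All three true: any error requires the gate to open, which has probability at most 0.05.
- Exactly one true: it is tested at no more than 0.05.
- None true: no type I error is possible.

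This is closed testing with Shaffer's logical restriction. The plan already needs it to justify 0.05 for FASTER versus SCOTT&EVA.

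**FWER over all three comparisons** (n = 87, 4 million replicates per scenario; standard error near 0.05 is √(0.05 × 0.95/4,000,000) ≈ 0.0001):

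| True state | Current rule | With release |
|---|---|---|
| All equal | 0.0496 | 0.0496 |
| SCOTT&EVA null, FASTER 0.4 | 0.0266 | 0.0398 |
| FASTER null, SCOTT&EVA 0.4 | 0.0267 | 0.0407 |
| SCOTT&EVA null, FASTER 2 | 0.0267 | 0.0500 |
| FASTER null, SCOTT&EVA 2 | 0.0266 | 0.0500 |
| Both 0.4 | 0.0482 | 0.0482 |
| Both 2 | 0.0500 | 0.0500 |

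With one null program, the current rule leaves about 0.05 − 0.027 = 0.023 unspent, nearly half the budget.

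**Power, both effects 0.4:**

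| Result | n = 87, current | n = 87, release | n = 90, current | n = 90, release |
|---|---|---|---|---|
| Both superior to TAU | 0.478 | 0.578 | 0.496 | 0.597 |
| SCOTT&EVA vs TAU | 0.660 | 0.705 | 0.675 | 0.721 |
| FASTER vs TAU | 0.616 | 0.671 | 0.632 | 0.687 |
| At least one | 0.798 | 0.798 | 0.811 | 0.811 |

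Here n = 90 is 120 × 0.75, the number left if drop-out is 25%.

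**If only one program works (0.4, n = 87).** Power to show it is 0.660 for SCOTT&EVA (0.661 with the release) or 0.616 for FASTER (0.617 with the release). The release hardly matters here.

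**The case against.** The strongest reply is that nothing here is an error. The single-step rule is valid, its level and sample size reproduce, and preferring a sharper valid rule is a matter of efficiency. That stands, and it sets the weight of the point.

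Second, a reader might take the opening sentence of Objectives {7} to mean that the trial must prove both programs, and so call it underpowered. The documents do not support that. The same section, Sample size {14} and the Analysis section all define success as at least one program superior to TAU, and on that criterion the change gains nothing.

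Third, using the unspent level has a price. With one program null and the other at 0.4, false rejection of the null program rises from 0.027 to about 0.040, and the chance of wrongly declaring both superior doubles from about 0.015 to about 0.030. Fixed local levels also give simple simultaneous intervals against TAU that match the tests; the stepwise rule does not. Both costs are real, but the first lies inside the error rate that the plan accepts, and the plan does not call for simultaneous intervals.

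Fourth, a reader might infer that the 0.80 is misreported. It is not: Sample size {14} defines it as power for at least one comparison, with both effects set at 0.4. Only the Discussion's summary drops these conditions.

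**Conclusion.** The point holds as an efficiency improvement to a valid procedure. Testing the remaining TAU comparison at 0.05 after the gate rejects everything that the present rule rejects and sometimes more, with strong FWER control. At the planning assumptions it adds 0.10 to the power to show both programs superior, and about 0.05 to each TAU comparison. At-least-one power, 87 per group and 360 in total do not move.

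Two further inferences fail. The present rule does not inflate type I error. Nor does the missing release cause the lower power when only one program works: that power is 0.62 to 0.66 at n = 87 (0.63 to 0.68 at n = 90) under either rule. The Discussion's wording is therefore a separate and minor matter.

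The figures rest on the protocol's effects, correlation and design effects and on normal approximations. FWER control of the stepwise rule requires each model-based test to hold its nominal level, as the current plan does too.

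**What to change.** In the Analysis section, state that if either TAU comparison is significant at the local level of 0.026632, the other TAU comparison and FASTER versus SCOTT&EVA are each tested at two-sided 0.05. Carry the same rule into the SAP, and settle it before database closure while the biometricians are still blinded.

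In the Discussion, say that 0.80 is the power for at least one rejection when both effects are 0.4, and add that it is about 0.62 to 0.66 at 87 per group if only one program works. Sample size {14} needs no correction on this point.

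The cost is a few sentences, plus whatever approval step the protocol's amendment section requires. No patients are added. The sponsor accepts the higher, still controlled, false-rejection rate shown above and gives up the match between the tests and simple simultaneous intervals against TAU.
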